### Outcomes

The primary outcome variable will be club attendance, which, for the designated fitness centers, will only reflect club visits with the intent to exercise and not access complementary services (i.e., spa, well-being centers, coffee lounges). This will be assessed across all trimesters, with particular emphasis on one-year results (as the primary outcome endpoint). Comparisons will be made over time within and across intervention conditions for both new members enrolling between September 1, 2025, and August 31, 2026, and members already enrolled prior to this period, for whom the intervention may reflect a change from their prior club experience. The secondary outcomes will be behavioral (attrition rate, namely the number of membership cancellations or dropouts as a percentage of the total number of new members in a given time period; see Methods section for details) and motivational constructs (exercise habit, intention to be physically active, satisfaction of basic psychological needs, behavioral regulation, enjoyment, and affective exercise experiences), in line with the study’s secondary hypotheses regarding potential motivational and behavioral changes associated with the intervention conditions. These will be assessed in a subsample of participants who will voluntarily take part in the longitudinal evaluations. Additional variables (i.e., state self-control, intensity agreement, course content evaluation, one-year pre-intervention attendance, and attrition patterns at the club level, and the degree and frequency of application of the knowledge provided during the training course) will be included for descriptive or exploratory tertiary analyses. No harm is expected from the intervention.

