### Statistical methods

Preliminary analyses will be conducted prior to all statistical procedures to examine data quality, missingness patterns, and identify potential violations of statistical assumptions. All analyses are planned to be performed using SPSS v.27.0 (IBM, Co.). The primary outcome of the study is attendance, which will be analyzed both for all fitness center members and separately for those who joined the clubs after the commencement of the study (i.e., after September 1, 2025). Attendance will be operationalized as the individual’s mean weekly attendance within each three-month interval and assessed at four time points during the 12 months of the study (three, six, nine, and twelve months). Primary analyses of attendance will be conducted using linear mixed-effects models (LMMs), with time specified as a within-subject factor and individuals treated as random effects to account for repeated observations. Intervention condition (control, SDT-based training, and hedonic-based training), time, and their interaction will be included as fixed effects, with age and sex included as covariates. These models will be used to characterize and descriptively compare attendance trajectories over time across intervention conditions, with emphasis on the magnitude and direction of longitudinal patterns rather than on individual-level causal inference. Primary analyses will follow an intention-to-treat principle adapted to the cluster-allocated design, such that all eligible individuals are analyzed according to their fitness center’s assigned condition, regardless of attendance patterns or dropout. Linear mixed-effects models were selected because they incorporate all available longitudinal observations under a missing-at-random assumption without requiring imputation.

Because intervention allocation occurs at the fitness-center level and each condition is implemented in a single center, cluster-level variance and intraclass correlation coefficients cannot be estimated independently of condition-related effects. Accordingly, comparisons across intervention conditions are considered exploratory and descriptive in nature. For complementary descriptive purposes, 3 (Condition) × 4 (Time Points) split-plot ANOVAs may be conducted to summarize overall patterns of longitudinal change in attendance. Results from these analyses will be interpreted descriptively, given that intervention conditions are implemented at the fitness-center level.

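### The primary attendance model has no pre-training value, so any stable club difference enters the 12-month and marginal-mean contrasts, while prior-year club data are left to tertiary description

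*Protocol article*

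**What the plan says.** The Statistical methods section fixes the primary model. Mean weekly attendance per quarter is "assessed at four time points during the 12 months of the study (three, six, nine, and twelve months"). Condition, "time, and their interaction will be included as fixed effects, with age and sex included as covariates", and the random part is "individuals treated as random effects to account for repeated observations". No pre-training value appears.

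The Outcomes section places the emphasis on the level at one year: "with particular emphasis on one-year results (as the primary outcome endpoint"). The same section lists "one-year pre-intervention attendance, and attrition patterns at the club level" among additional variables that "will be included for descriptive or exploratory tertiary analyses".

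The plan is open about the main limitation. Because each condition has one club, it says that club variance cannot be separated from condition and that "comparisons across intervention conditions are considered exploratory and descriptive in nature". It will nevertheless report slope differences and estimated marginal means with 95% confidence intervals. The Objectives predict better attendance than control in both trained clubs, and higher attendance under the hedonic course than under the SDT course.

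**The concern.** Three clubs in different places will differ in usual attendance for reasons unrelated to training. With one club per condition, age and sex are the only adjustment standing between such differences and the condition contrast. The information that speaks most directly to a club's usual level and season is that club's own previous year. The plan names that information and then keeps it out of the primary comparison.

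The slope contrast only partly fills the gap. The courses are held at the start of September, so the first modelled value (the mean of months 0–3) is already post-training. The Objectives expect the hedonic course to do better partly because it can be applied easily and at once. An effect of that shape lies largely inside the first value and leaves little slope difference. It would then show only as a level difference, which is where a standing club difference also shows.

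At stake is a one-year difference with a narrow interval, since the clubs have many members, that reflects which club it was and not which course was given.

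**Working it through.** **The plan's own figures.** No power or precision is stated for the attendance comparison. The only sample size concerns the motivational subsample (f = 0.20, α = 0.05, power 0.95, three measurements, r = 0.70, ε = 0.70). The repeated-measures calculation reproduces 53 completers (power 0.953), and 53/0.45 = 117.8 against the stated 117 or so. Neither figure bears on this point.

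**Which contrast carries the club difference.** Write the mean of club k in quarter q as a + c_k + s_q + δ_k(q), where c_k is the stable club level, s_q the shared season and δ_k the training effect (zero in control).

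- 12-month contrast: (c_1 − c_0) + δ(4). The club difference enters in full.
- Change from quarter 1 to quarter 4: δ(4) − δ(1). The club difference cancels, but so does a constant δ.
- Change from the same quarter a year earlier: δ(4) plus any club-by-year deviation. The stable difference cancels and an immediate effect is kept.

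**Simulation.** Assumed: 200 members per club, member SD 0.8 and residual SD 0.6 (total 1.0), club gap 0.20 visits/week, no training effect, 40 replicates, age and sex omitted. Mean results:

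| Contrast | Estimate |
|---|---|
| Mean over four quarters | 0.196 |
| 12 months | 0.202 |
| Condition-by-time slope | 0.002 |
| 12 months minus own pre-period | 0.022 |

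The last has a Monte Carlo standard error of 0.089/√40 = 0.014, so it is compatible with zero. It uses each member's own earlier value, as is possible for existing members.

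**How often a club gap looks like an effect.** The documents give no attendance SD or club difference. Assume individual SD 1.0–1.5 and a gap of 0.1–0.3 visits/week, with SE = SD·√(2/n). The nominal 95% interval for the level contrast excludes zero in 10–85% of trials at 200 members per club (SE 0.100–0.150) and in 56–100% at 2,000 (SE 0.032–0.047). More members make the false signal firmer.

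**What the prior-season contrast gains for new members.** Assume between-club SD τ = 0.15, individual SD s, year-to-year correlation of club means ρ, and independent cohorts of n per club each year.

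- Post-only variance: 2(τ² + s²/n)
- Change-contrast variance: 4(1 − ρ)τ² + 4s²/n
- Break-even: ρ = 0.5 + (s²/n)/(2τ²)

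At n = 200:

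| s | Post-only SD | Change SD, ρ = 0.8 | Change SD, ρ = 0.9 | Break-even ρ |
|---|---|---|---|---|
| 1.0 | √0.0550 = 0.235 | √0.0380 = 0.195 (−17%) | √0.0290 = 0.170 (−27%) | 0.61 |
| 1.5 | √0.0675 = 0.260 | √0.0630 = 0.251 (−3%) | √0.0540 = 0.232 (−11%) | 0.75 |

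If the 55% attrition in the Sample size section applied to the September cohort, n = 200 × 0.45 = 90. Break-even is then 0.75 at s = 1.0. At s = 1.5 it is 0.5 + 0.025/0.045 = 1.06, so the change contrast is noisier at every correlation.

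**The case against.** The strongest reply has four parts.

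- **The plan already concedes the confounding** and calls the comparison descriptive, so the prior-year data have much the same standing as the primary contrast. This stands as far as the label goes: nothing is concealed, and the change is partly one of emphasis. It does not answer the point that a descriptive level contrast can be made less misleading with data the plan itself names.
- **Slopes are a reported effect measure**, the main hypothesis concerns the course of attendance, and the SDT course is expected to act slowly. This stands. A reader might infer that club differences spoil every condition comparison; the slope result of 0.002 shows that they do not. The slope remains blind to an early, constant effect and open to seasonal patterns that differ between clubs.
- **Precision.** A reader might infer a large gain from differencing. If club means were known exactly, the SD would fall by 37–55%, with break-even at a correlation of 0.5. That ignores sampling error and does not hold for the September new-member cohort.
- **Data.** The documents mention club-level patterns, historical enrolment records and electronic tracking. They do not say that individual records by joining date for 2024/25 are held. This stands, and the fix allows for it.

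**Conclusion.** The point holds for the 12-month and marginal-mean contrasts: a stable club difference enters them one for one, and the plan has no term that could remove it. It does not hold for the condition-by-time slope, which is free of a constant offset but cannot recover an effect complete within the first quarter.

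The algebra needs no assumption beyond additivity. The sizes rest on assumed inputs: individual SD 1.0–1.5, club gaps of 0.1–0.3, between-club SD 0.15 and year-to-year correlations of 0.8–0.9.

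Two stronger conclusions are not supported. One is that a difference-in-differences should be the sole primary estimate for new members: they have no attendance of their own before joining, so the contrast compares different people across years, and in small cohorts it may add more noise than it removes. The other is that the prior year would let the trial attribute a difference to the training: with one club per condition, anything that changed in one club in 2025/26 remains inseparable from its course.

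**What to change.** 1. **Already-enrolled members:** enter each member's own pre-September attendance in the attendance model, as a baseline time point or a covariate.
2. **New members and attrition:** beside the planned level contrast, report the same-quarter change from the same club's 2024/25 season, intervention club minus control club. Use the previous new-member cohort at equal membership duration if the extract allows, otherwise club-level values. Apply the same counting rules in both seasons, and plot both seasons by club.
3. **Interpretation:** state in advance that a level difference will not be read as favouring a condition unless the prior-season contrast agrees. Keep the descriptive label.

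Cost: changed analysis wording, possibly one further extract from the electronic system, and the ethics approval that the protocol requires for amendments. The new-member change contrast carries √2 times the sampling error of the level contrast when cohorts are of equal size (0.14–0.21 against 0.10–0.15 at 200 per club), which is why it is placed beside the planned contrast and does not replace it.

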### Participant timeline

The study is expected to run between September 2025 and the end of August 2026. The three health clubs will be randomized to the conditions (i.e., control, experimental 1 [SDT-based course], and experimental 2 [hedonic-based course]) at the beginning of this period. Baseline motivation and behavior assessments will be conducted upon enrollment after verification of the inclusion and exclusion criteria. These variables will be assessed again at six and 12 months post-randomization. The training courses will be held at the beginning of September at each club according to the conditions previously randomized. Thereafter, short, individualized discussions with each of the exercise professionals, focusing on reinforcing the ideas presented at the initial training courses and providing support for implementation, will take place approximately 10 to 12 weeks apart until the end of August 2026. The application of the content knowledge delivered during the respective training courses (i.e., frequency and fidelity of implementation) will be assessed during each visit. Attendance and dropout data will be collected continuously. Table 1 presents the participant timeline and sequencing of recruitment, allocation, intervention, and assessments.

**Table 1 tab1:** Participants’ enrollment, allocation, post-allocation, and close-out timeline.

	Study period						
	Enrollment	Allocation	Post-allocation				Close-out
Timepoint	-t1	0	t1	t2	t3	t4	t5
Enrollment							
Eligibility screen	⨯						
Informed consent	⨯						
Allocation (of the clubs)		⨯					
Interventions							
Control			⨯	⨯	⨯	⨯	
Experimental (I)—SDT			⨯	⨯	⨯	⨯	
Experimental (II)—hedonic			⨯	⨯	⨯	⨯	
Assessments							
Club’s members							
New memberships			⨯	⨯	⨯	⨯	⨯
Dropouts			⨯	⨯	⨯	⨯	⨯
Exercise frequency			⨯	⨯	⨯	⨯	⨯
Exerciser’s sample							
Sociodemographic	⨯						
Behavioral regulations	⨯				⨯		⨯
Basic psychological needs	⨯				⨯		⨯
Exercise enjoyment	⨯				⨯		⨯
Attraction-antipathy	⨯				⨯		⨯
Pleasure-displeasure	⨯				⨯		⨯
Preference/Tolerance	⨯				⨯*		⨯*
Exercise habit	⨯				⨯		⨯
Intention to be physically active	⨯				⨯		⨯
State self-control	⨯				⨯		⨯
Professionals							
Course comprehension test			⨯				
Course knowledge application				⨯	⨯	⨯	⨯

t1 = Baseline assessments; t2 = 3 months; t3 = 6 months; t4 = 9 months; t5 = 12 months; * = only agreement items.

### Sample size

Sample size determination follows SPIRIT (Chan et al., 2025) guidance for pragmatic interventions in which traditional power calculations are constrained by design features. As such, considerations were made while considering the nature of the intervention, the fitness-center–level allocation of training conditions, and the longitudinal structure of the primary outcome. Given that only three centers are included, formal power calculations for between-condition hypothesis testing based on individual-level randomization are not appropriate. Instead, sample size adequacy is primarily related to the large number of individual observations and repeated measurements, which support the longitudinal estimation of attendance trajectories over time within the constraints of the present pragmatic design.

For the primary outcome (attendance), all eligible members of the participating fitness centers will be included in the analyses at three, six, nine, and 12 months, although the focus will be given to those enrolled after September 1, 2025. Each participating fitness center has more than 2,000 enrolled members at any given time, and historical records indicate that approximately 200 new members typically enroll in each club during the month of September. This provides a high-density longitudinal dataset, with multiple repeated observations per individual and sufficient sample size in each intervention condition to support longitudinal mixed-effects modeling of attendance trajectories.

As for the secondary outcomes, these will focus on (i) dropout rates at three-month intervals up until one year, and (ii) motivational variables. In the case of dropout rates, administrative records from all members enrolling after September 1, 2025, will be used. This outcome is derived from the complete population of new members during the intervention period, and the expected number of observed events over the 12-month follow-up is sufficient to support descriptive and time-to-event analyses of attrition patterns across intervention conditions. In the case of the motivational variables, the most restrictive analyses will be conducted in a subsample of exercisers enrolling in September. These participants will be recruited for the longitudinal assessment of behavioral regulation, satisfaction of basic psychological needs, exercise enjoyment, subjective exercise experience, exercise habit, and intention to be physically active, assessed at baseline, six months, and twelve months. Sample size considerations for this subsample were guided by the most restrictive planned within-participant longitudinal comparisons and estimated using G*Power (v.3.1.9.7) (Faul et al., 2009). Using benchmarks from a related work [e.g. (Teixeira et al., 2023; Andrade et al., 2022; Henriques et al., 2023)], a repeated-measures ANOVA assuming a small-to-moderate magnitude of change over time (*f* = 0.20), an *α* level of 0.05, statistical power (1-*β*) of 0.95, three repeated measurements, a correlation between repeated measurements of approximately r = 0.70, and allowing for potential violations of sphericity (*ε* ≈ 0.70), a minimum of approximately 53 participants completing follow-up assessments across the three fitness centers is expected to provide adequate sensitivity to characterize meaningful longitudinal changes in motivational outcomes over time. Linear mixed-effects models will be used for analysis, as they are expected to be at least as efficient as the repeated-measures assumptions used for these calculations and allow the inclusion of all available data in the presence of missing observations. Given that the average attrition rate in Portugal over a one-year period in these contexts has been reported as ranging between 50 and 60% (Pedragosa and Ferreira, 2024), a total sample of approximately 117 participants (≈55% attrition) will be required.

### Recruitment, allocation, and blinding

The health clubs were selected due to their standardized business practices across all clubs (thus reducing potential bias associated with heterogeneity). Also, all clubs have an electronic tracking system that allows the monitoring of attendance, specifically in the designated exercise areas. The control and experimental groups will be allocated through a simple randomization procedure performed by the primary investigator using the tool provided by randomizer.org. Because all centers were allocated simultaneously prior to intervention implementation, no separate allocation concealment procedure was performed. Newly enrolled members will be recruited on a voluntary basis in all clubs through information that will be provided at the reception desks and by the sales teams at the time of registration. The recruitment of new members will occur only during the month of September on a rolling basis. A personal training session will be offered to all those who agree to participate in the three assessments of the study. Exercise professionals were aware that they were participating in a study involving professional training and follow-up reinforcement sessions related to exercise promotion and communication strategies. However, they were not informed of the specific study hypotheses linking the training contents to longitudinal attendance, attrition, and motivational outcomes among exercisers. From the professionals’ perspective, the intervention was presented primarily as a professional-development opportunity intended to support evidence-informed exercise-promotion practices. Exercisers participating in the longitudinal assessments were unaware of intervention allocation and of the specific hypotheses being examined. They were informed only that the study aimed to assess the longitudinal development of motivational and behavioral variables associated with exercise participation. Due to their role in intervention delivery and study coordination, the research team could not be considered blinded to intervention allocation. However, the primary attendance and dropout outcomes were obtained from administrative fitness-center records, thereby reducing the potential influence of participant expectancy effects on the primary outcome measures. Nevertheless, because exercise professionals were aware of the training content they received, the possibility of performance-related influences on professional behavior cannot be fully excluded and will be considered when interpreting future outcome findings.

### Data collection methods

#### Participants (fitness club members)

##### Basic psychological needs

The Portuguese version of the Basic Psychological Need Satisfaction and Frustration Scale in Exercise (BPNSFS-E) (Rodrigues et al., 2019) will be used. This instrument includes 24 items, 12 assessing need satisfaction and 12 assessing need frustration, which are theoretically aligned with constructs from SDT (Vansteenkiste et al., 2020). The scale evaluates satisfaction of autonomy (e.g., “I have a feeling of freedom and choice in the things I make”), competence (e.g., “I feel confident that I can do things right”), and relatedness (e.g., “I feel that the people I care for also care for me”), as well as frustration of autonomy (e.g., “I feel the majority of the things I do are out of obligation”), competence (e.g., “I feel insecure about my abilities”), and relatedness (e.g., “I feel excluded from the group I want to belong to”). Responses are provided on a 5-point Likert scale ranging from 1 (“Totally disagree”) to 5 (“Totally agree”).

##### Behavioral regulations

The Portuguese version of the Behavioral Regulation in Exercise Questionnaire (BREQ-4) (Teixeira et al., 2022b) will be used to assess behavioral regulation according to the organismic integration sub-theory of SDT (Ryan and Deci, 2017). This instrument includes 28 items covering all behavioral regulations, including the dual facets of introjected regulation: (e.g., amotivation: “I do not see why I should have to exercise”; external regulation: “I exercise because other people say I should”; introjected avoidance regulation: “I feel guilty when I do not exercise”; introjected approach regulation: “I feel proud of myself when I persist”; identified regulation: “I value the benefits of exercise”; integrated regulation: “I exercise because it is consistent with life goals”; and intrinsic motivation: “I exercise because it’s fun.”) Responses are provided on a 5-point Likert scale ranging from 0 (“Not true for me”) to 4 (“Very true for me”). The 21-item version that demonstrated the best model fit in this context will be employed (Teixeira et al., 2022b).

